## Abstract

**Background:**

The goals of intentional curative pediatric epilepsy surgery are to achieve seizure-freedom and antiepileptic drug (AED) freedom. Retrospective cohort studies have indicated that early postoperative AED withdrawal unmasks incomplete surgical success and AED dependency sooner, but not at the cost of long-term seizure outcome. Moreover, AED withdrawal seemed to improve cognitive outcome. A randomized trial is needed to confirm these findings. We hypothesized that early AED withdrawal in children is not only safe, but also beneficial with respect to cognitive functioning.

**Design:**

This is a multi-center pragmatic randomized clinical trial to investigate whether early AED withdrawal improves cognitive function, in terms of attention, executive function and intelligence, quality of life and behavior, and to confirm safety in terms of eventual seizure freedom, seizure recurrences and “seizure and AED freedom.” Patients will be randomly allocated in parallel groups (1:1) to either early or late AED withdrawal. Randomization will be concealed and stratified for preoperative IQ and medical center. In the early withdrawal arm reduction of AEDs will start 4 months after surgery, while in the late withdrawal arm reduction starts 12 months after surgery, with intended complete cessation of drugs after 12 and 20 months respectively. Cognitive outcome measurements will be performed preoperatively, and at 1 and 2 years following surgery, and consist of assessment of attention and executive functioning using the EpiTrack Junior test and intelligence expressed as IQ (Wechsler Intelligence Scales). Seizure outcomes will be assessed at 24 months after surgery, and at 20 months following start of AED reduction. We aim to randomize 180 patients who underwent anticipated curative epilepsy surgery below 16 years of age, were able to perform the EpiTrack Junior test preoperatively, and have no predictors of poor postoperative seizure prognosis (multifocal magnetic resonance imaging (MRI) abnormalities, incomplete resection of the lesion, epileptic postoperative electroencephalogram (EEG) abnormalities, or more than three AEDs at the time of surgery).

**Discussion:**

Growing experience with epilepsy surgery has changed the view towards postoperative medication policy. In a European collaboration, we designed a multi-center pragmatic randomized clinical trial comparing early with late AED withdrawal to investigate benefits and safety of early AED withdrawal. The TTS trial is supported by the Dutch Epilepsy Fund (NL 08-10) ISRCTN88423240/ 08/05/2013.

## Background

For children with refractory epilepsy, epilepsy surgery is a successful and widely accepted therapeutic option with postoperative seizure freedom rates ranging from 41 to 93 % [1, 2]. In patients who have been operated on and who have reached seizure freedom the ultimate goal is to discontinue antiepileptic drug (AED) use and to improve developmental capacities [3–5]. AEDs are known to have cognitive side-effects, particularly in children. Most affected cognitive functions are attention, vigilance and psychomotor speed [6–9]. AED reduction has been reported to improve cognitive processing under time pressure [8, 10], psychomotor speed and alertness [11–13], processing speed [14], verbal memory [15] and Intelligence Quotient (IQ) [9]. The growing body of evidence that cognitive functioning improves after AED withdrawal has increased awareness of the possible benefits of the earliest possible withdrawal of AEDs after epilepsy surgery. Two recently published studies [16, 17] showed that early withdrawal of drug treatment unmasks incomplete surgical success and AED dependency sooner, but not at the cost of worse long-term seizure outcome. Thus, early AED withdrawal would discern the few that require further AEDs from the many that can safely stop, without changing the chance of regaining seizure freedom. A pressing question is whether early AED withdrawal improves cognitive outcome measures, as compared to current care with usually later AED withdrawal. To answer that question we designed a pragmatic randomized clinical trial to investigate the benefits and safety of early AED withdrawal after epilepsy surgery in children. We hypothesize that 1) children who discontinue AED’s early have better cognitive scores, behavior and quality of life than those who discontinue late, particularly at 1 year after surgery (when 1 group is without AEDs and the other is still on AEDs), and maybe persisting from then on, and 2) early AED withdrawal is safe and does not cause more recurrences that are unresponsive to restart of medication, than late withdrawal.

### Study objectives

The primary objective is to investigate whether early AED withdrawal improves cognitive function, in terms of attention and executive functions, compared to late AED reduction. The secondary objectives are to assess (improvement in) IQ, and safety, in terms of seizure recurrences, long-term seizure freedom and “seizure and AED freedom” of early versus late AED withdrawal. Seizure freedom will be defined as complete seizure freedom (including auras), expressed as Engel 1A or ILAE class 1 for at least 1 year [18, 19], and “seizure and AED freedom” as being seizure free without medication for at least 1 year. In addition, we will compare behavior, quality of life and other neuropsychological outcomes between the two AED withdrawal strategies.

## Methods/Design

### Study design

The TimeToStop trial will be a European multicenter pragmatic randomized clinical trial. In the Netherlands the trial has been approved by the Medical Ethical Committee of the University Medical Center Utrecht, which is the leading ethical committee. Other participating centers are in the process of protocol submission and have not yet obtained definite approval. Only then, local patient recruitment will start. For every patient who will be included in the trial we will obtain informed consent. In the TimeToStop trial, index intervention is early withdrawal: AED withdrawal is started 4 months after surgery and completed within 8 months after start of withdrawal (thus, at latest 12 months postoperatively). Reference intervention is late AED withdrawal: tapering off medication starts at 12 months after surgery and completion should be within 20 months after surgery. For both treatment arms, the total tapering period is set at 8 months maximum and clinicians may decide which AED they want to taper first and at what speed they will reduce each individual drug. A tapering period of 8 months is considered reasonable, as from the retrospective TimeToStop (TTS) study [16] it could be calculated that patients who fulfill the inclusion criteria used on average 1.7 AEDs prior to surgery (range 0–3). The late (reference) starting point of AED tapering – i.e. 12 months – is based on current practice; the median interval between surgery and drug reduction in our retrospective European study was 12.5 months [16]. The 4 months’ time-point in the early withdrawal group is selected mainly because of logistical reasons. First, informing parents and recruiting patients needs time. Second, inclusion requires proof of early surgical success, which needs a certain time window to discriminate between acute postoperative (running-down) seizures and true seizure recurrence. Third, in some children clinicians may want to prove completeness of resection by performing a postoperative magnetic resonance imaging (MRI), for which a minimum follow-up time of a few months is required. For both intervention strategies, the treating physician is allowed to start tapering earlier if patients experience unacceptable side effects of prescribed AEDs. Rescue medication that is started preoperatively and withdrawn shortly after surgery, can be discontinued according to existing local routine practice, and will not be investigated in this study.

The trial’s primary outcome measure at 1 year after surgery is cognitive functioning, in terms of attention and executive functioning, which will be assessed using the EpiTrack Junior [20]. As secondary cognitive outcome measure, intelligence will be tested with the Wechsler Preschool and Primary Scales, the Wechsler Intelligence Scale for children, or the Wechsler Adult Intelligence scale, depending on the children’s age and capabilities; scores derived are Verbal (VIQ), Performal (PIQ) and Full-scale IQ, perceptual organization or reasoning and information processing speed index scores. We will measure baseline neuropsychological status maximum 3 months before surgery (t1), and thereafter at 12 months (±2 months) (t2) and 24 months (±2 months) (t3) postoperatively. Patients and/or parents will at all neuropsychological test points complete three types of questionnaires to assess the secondary outcome measures: the Child Behavior Checklist (CBCL) and the the Hague Side Effects Scale (HASES) [21] will be completed by the parents, and the Pediatric Quality of Life Inventory^TM^ (PedsQL™) will be completed by both parents and patients. This design will allow us to assess whether cognitive performance is better in the early AED-withdrawal group, with patients being AED-free at 1 year following surgery, compared to the group that is still on full medication at the first postoperative time point. It will also enable the study of differences at a later follow-up time point, when both groups have completely discontinued medication (t3) (Fig. 1). Seizure outcome will be assessed at the moment of randomization, as seizure freedom is an inclusion criterion, at 24 months after surgery, and at 20 months following start of AED withdrawal. This design allows us to assess differences in seizure outcome at equal AED-free intervals for both groups, and at 2 years after surgery irrespective of length of AED freedom.

**Fig. 1 Fig1:**
[figure not shown]
Trial design. Flowchart of trial design; NPA, neuropsychological assessment

Patients will be allocated to treatment strategy by concealed blocked randomization and randomization will be stratified for preoperative IQ score and medical center. The primary goal of randomization is to achieve an AED treatment duration contrast. Therefore, physicians and patients allocated to an arm will be instructed to comply with that strategy. However, these intervention strategies will to a certain extent be in compliance with clinical practice, and allow “protocol violations” for the following instances: if patients have seizure recurrences in the period before scheduled AED withdrawal, they do not have to start AED withdrawal. The same applies to seizure recurrences that occur after start of tapering medication. Patients can restart medication and do not have to taper medication again, regardless of planned medication status. Notably, whatever “protocol deviations” will occur, patients will be analyzed as randomized (intention-to-treat principle).

### Inclusion criteria

In order to be eligible a subject must meet all of the following criteria:Younger than 16 years at surgery, with focal non-idiopathic epilepsyNative speaker in the language in which the neuropsychological tests have to be takenAble to perform an EpiTrack Junior [20] test preoperativelyUnderwent intentionally curative epilepsy surgeryAfter surgery, the treating physician considers withdrawal of AEDs, with the intention to completely discontinue medicationThe treating physician, the patient (if capable), and the parents agree with randomization in either arm of the studyPostoperative seizure freedom was achieved (with the exception of so-called running down seizures not outlasting 2 weeks)Written informed consent of children and both parents or caregivers of children older than 12 years, and of both parents or caregivers of children below that age

### Exclusion criteria

A subject who meets any of the following criteria will be excluded from participation:A contraindication to be randomized to either of the two withdrawal strategiesThe treating physician does not want to discontinue all AEDs within a maximum time frame of 8 months as prescribed in the study protocolMultifocal MRI abnormalities, known incomplete resection of the anatomical or epileptogenic lesion certified before randomization (if considered necessary by the treating physician a postoperative MRI may be performed) and, if a postoperative electroencephalogram (EEG) is performed before randomization (at the discretion of the treating physician), epileptic EEG abnormalities. These are the most important risk factors of seizure recurrence or unfavorable long-term seizure outcome [16]Use of more than three AEDs at the time of surgery. The reason is that clinicians can then not be expected to want to wait for 12 months in the late withdrawal arm to reduce the first AED in these patients. Furthermore, withdrawing 4 or more AEDs within 8 months may be difficult to achievePatients who are on a ketogenic diet or have a vagal nerve stimulator implantedIf surgery is primarily intended as “tumor surgery” (a growing epileptogenic lesion was the indication for surgery) and not as epilepsy surgery

#### Excluded patients

Participating centers will provide brief anonymized information about all children who are operated on, including those who were not in the trial, to document reasons for exclusion and the overall proportion of eligible patients, allowing the assessment of generalizability of the trial results. We will only report aggregated data of excluded patients.

### Statistical analysis

The general approach towards analysis will be on an intention-to-treat basis, so patients randomized will be analyzed and accounted for as allocated, independent of later compliance.

For all analyses described below, we will add baseline adjusted analyses using various regression techniques (linear regression for continuous and logistic regression for binary outcomes). For these adjustments to increase statistical precision, we will use propensity score methods or inverse variance weighting methods.

Prior to analyses described below, we will deal with missing values by formal accepted multiple imputation methods, for reasons of optimizing statistical precision but more importantly because particularly loss to follow-up may be expected not to occur randomly in this trial.

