#### Outcome parameters

Cognitive outcome: differences in EpiTrack scores, IQ scores and other continuous outcome measures of neuropsychological assessment will be analyzed using independent samples *t*-tests or other tests depending on distributions. EpiTrack and IQ differences will be assessed cross-sectionally to answer the primary research question. Additionally, longitudinal changes in EpiTrack measures and IQ compared to preoperatively will be assessed between both treatment arms using linear mixed models. We will calculate a number needed to treat, expressed as the number of patients required to taper drugs earlier to achieve one more patient with improvement in attention. Analyses will be considered statistically significant if 95 % confidence intervals for group differences do not include 0, compatible with a 2-sided *p* < 0.05. For chances of eventual seizure freedom and “seizure and AED freedom”; we will calculate a relative risk and a risk difference with 95 % confidence intervals. Chances of eventual seizure freedom and “seizure and AED freedom” will be compared between the groups at 24 months after surgery and at 20 months following start of AED withdrawal; for the early withdrawal arm this will be at 24 months and for the late withdrawal arm at 32 months.

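### The tools named for gaining precision in the added baseline-adjusted analyses can leave most of that gain out of the reported intervals; direct covariate adjustment would keep it

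*Protocol article*

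**What the plan says.** The article's Statistical analysis section states, for all the analyses that follow it, "we will add baseline adjusted analyses using various regression techniques (linear regression for continuous and logistic regression for binary outcomes"). The next sentence gives the aim and the means: "For these adjustments to increase statistical precision, we will use propensity score methods or inverse variance weighting methods". It names no covariates, no way of using the propensity score (weight, covariate or strata) and no variance estimator.

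Under Outcome parameters, the continuous neuropsychological outcomes "will be analyzed using independent samples *t*-tests or other tests depending on distributions", and "EpiTrack and IQ differences will be assessed cross-sectionally to answer the primary research question". The main comparison is therefore unadjusted, and the adjusted analyses come on top of it. Significance is read from intervals: "Analyses will be considered statistically significant if 95 % confidence intervals for group differences do not include 0".

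The material for direct adjustment is already collected. Study design places a neuropsychological assessment within the 3 months before surgery, and "randomization will be stratified for preoperative IQ score and medical center". Allocation is 1:1.

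**The concern.** In a 1:1 randomised trial the propensity score is known by design, so there is no confounding by indication to remove. Baseline adjustment is useful here because the preoperative score predicts the later score. A propensity model predicts allocation, not outcome. Fitting it does balance chance differences between the arms, so the estimate becomes less variable. The usual standard errors treat the fitted score as known, however, and do not fall with it. Because this plan reads significance from 95% intervals, precision that does not reach the interval is lost to inference.

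Inverse variance weighting, in its ordinary sense, weights observations or estimates by the inverse of their variance. It does not draw on a child's own baseline score, so it does not do what the sentence asks of it.

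At stake is the sensitivity of the adjusted results for EpiTrack, IQ, behavior and quality of life.

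**Working it through.** **Inputs.** From Sample size calculation: 75 per arm, SD 4.70, difference 2.16, two-sided alpha 0.05, power 0.80. The correlation ρ between preoperative and postoperative score is not in the document; it is assumed at 0.3, 0.5 and 0.7.

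**Step 1: the plan's own figure.** Unadjusted SE = 4.70 × √(2/75) = 0.7675. Power = Φ(2.16/0.7675 − 1.96) = Φ(0.854) = 0.804. The stated 75 per arm is reproduced.

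**Step 2: direct adjustment.** SE = 0.7675 × √(1 − ρ²); power = Φ(2.16/SE − 1.96).

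**Step 3: propensity weighting with an ordinary SE.** To a good approximation the true SE is that of step 2, while the reported SE stays at 0.7675. The interval half-width is then 1.96 × 0.7675 = 1.504. Power = Φ((2.16 − 1.504)/true SE). Coverage = P(|Z| < 1.504/true SE).

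| ρ | true SE | power, direct | power, weighting with ordinary SE | coverage, weighting |
|---|---|---|---|---|
| 0.3 | 0.732 | 0.839 | 0.815 | 0.960 |
| 0.5 | 0.665 | 0.901 | 0.838 | 0.976 |
| 0.7 | 0.548 | 0.976 | 0.884 | 0.994 |

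**Step 4: simulation check** (3,000 trials per setting, same inputs; the propensity model uses the baseline score alone, or the baseline score plus four further baseline variables unrelated to outcome).

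| Setting | Method | Empirical SE | Mean reported SE | Coverage | Power |
|---|---|---|---|---|---|
| ρ 0.5, baseline only | direct covariate | 0.674 | 0.666 | 0.944 | 0.892 |
| | weighting, robust SE | 0.674 | 0.770 | 0.975 | 0.830 |
| | weighting, corrected SE | 0.674 | 0.665 | 0.945 | 0.893 |
| | score as covariate | 0.674 | 0.666 | 0.945 | 0.892 |
| ρ 0.5, baseline + 4 | direct covariates | 0.678 | 0.676 | 0.950 | 0.892 |
| | weighting, robust SE | 0.679 | 0.781 | 0.972 | 0.816 |
| | weighting, corrected SE | 0.679 | 0.674 | 0.948 | 0.890 |
| | score as covariate | 0.678 | 0.761 | 0.969 | 0.833 |
| ρ 0.7, baseline only | direct covariate | 0.555 | 0.549 | 0.947 | 0.973 |
| | weighting, robust SE | 0.555 | 0.772 | 0.992 | 0.872 |

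The corrected SE allows for estimation of the score. At ρ 0.3 with five variables, power is 0.824 for direct adjustment and 0.801 for weighting with robust SE, a gap of 2.3 points.

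**Reading.** Within each setting the empirical SEs agree, so the weighted estimate itself gains the precision. Only the reported SE differs. With robust SEs, weighted intervals are 1.006 to 1.024 times the unadjusted width at ρ 0.5 and 0.7. The score as a covariate matches direct adjustment when baseline is the only variable in it, and loses part of the gain when several variables enter.

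**The case against.** The strongest reply is that the loss comes from a standard error the article does not specify. With a variance that allows for the estimated score, weighting equals direct adjustment, and an analysis plan that is not shown may well say so. This stands: the loss is a risk of the plan as worded, not a certainty. A reader might infer that propensity scores inherently give over-wide intervals in a randomised trial. The calculations do not support that.

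A reader might also infer that the trial has less power than it claims. It does not. The 80% belongs to the unadjusted comparison, and every propensity figure above is at or above that level.

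Three further points stand in part:

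- The same section names linear regression, which would keep the gain if baseline scores were entered directly. The following sentence, however, assigns the precision gain to other tools.
- Pooling stratum-specific differences by inverse variance would adjust for the strata, including preoperative IQ. It would still not use the child's own preoperative score on the outcome.
- Direct adjustment has its own cost. With ten assumed, non-prognostic centers and an IQ stratum also entered, power at ρ 0.5 was about 87%, not 89%. Sparse centers therefore need some care.

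Finally, removing weighting everywhere would go too far. The article reports relative risks and risk differences for seizure outcomes. Weighting gives these directly, whereas logistic regression gives odds ratios.

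**Conclusion.** The point holds as a modest improvement that costs nothing in data. The sentence sets precision as the aim, then names one method that does not use the child's baseline score and another that brings the gain into the interval only under conditions the text does not state.

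If weighting with the usual robust standard error is used, the shortfall against direct adjustment is about 6 to 8 points of power at ρ 0.5 (0.830 against 0.892; 0.816 against 0.892), about 10 at ρ 0.7 (0.872 against 0.973) and 2 to 3 at ρ 0.3. These sizes rest on the assumed correlation, on 75 analysed per arm and on a linear relation between baseline and outcome.

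The error is conservative: intervals over-cover and do not produce false positives. It is confined to the supplementary adjusted analyses of continuous outcomes. The primary t-test, its sample size and its power are unaffected.

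**What to change.** For continuous outcomes, replace the sentence with wording such as: the adjusted analyses will be linear regressions with the preoperative value of that outcome, preoperative IQ stratum and medical center as covariates, small centers being pooled if needed. This takes the place of propensity score and inverse variance weighting for those outcomes.

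If weighting is kept, for example to estimate adjusted risk differences for the binary seizure outcomes, call it inverse probability weighting and state that the variance allows for estimation of the score.

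The cost is one or two sentences. No new data are needed, the sample size does not change, and the choice between two different methods is settled before the data are seen.

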#### Outcome parameters

Cognitive outcome: differences in EpiTrack scores, IQ scores and other continuous outcome measures of neuropsychological assessment will be analyzed using independent samples *t*-tests or other tests depending on distributions. EpiTrack and IQ differences will be assessed cross-sectionally to answer the primary research question. Additionally, longitudinal changes in EpiTrack measures and IQ compared to preoperatively will be assessed between both treatment arms using linear mixed models. We will calculate a number needed to treat, expressed as the number of patients required to taper drugs earlier to achieve one more patient with improvement in attention. Analyses will be considered statistically significant if 95 % confidence intervals for group differences do not include 0, compatible with a 2-sided *p* < 0.05. For chances of eventual seizure freedom and “seizure and AED freedom”; we will calculate a relative risk and a risk difference with 95 % confidence intervals. Chances of eventual seizure freedom and “seizure and AED freedom” will be compared between the groups at 24 months after surgery and at 20 months following start of AED withdrawal; for the early withdrawal arm this will be at 24 months and for the late withdrawal arm at 32 months.

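### The primary EpiTrack Junior comparison is an unadjusted t-test, although baseline score and stratification factors are collected: valid and correctly powered, but it forgoes available precision

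*Protocol article*

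**What the plan says.** Under Outcome parameters, the protocol article states that EpiTrack scores, IQ and "other continuous outcome measures of neuropsychological assessment will be analyzed using independent samples" t-tests, with another test allowed where the distribution requires it. It then names the comparison that decides the trial: "EpiTrack and IQ differences will be assessed cross-sectionally to answer the primary research question". No covariate is mentioned for that comparison.

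Adjustment appears in two other places:
- Statistical analysis: "For all analyses described below, we will add baseline adjusted analyses using various regression techniques", with linear regression named for continuous outcomes. The next sentence gives the purpose and the method: "For these adjustments to increase statistical precision, we will use propensity score methods or inverse variance weighting methods".
- Outcome parameters: "Additionally, longitudinal changes in EpiTrack measures and IQ compared to preoperatively will be assessed between both treatment arms using linear mixed models".

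The covariates are available. Study design says "We will measure baseline neuropsychological status maximum 3 months before surgery (t1"), and Inclusion criteria requires that the child could do the EpiTrack Junior before surgery. The allocation text below Fig. 1 says "randomization will be stratified for preoperative IQ score and medical center".

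Sample size calculation uses the full SD of 4.70 with no allowance for baseline adjustment.

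**The concern.** A preoperative measurement of the outcome is usually among the better predictors of the later score. Here it is obtained in every eligible child, yet the test that answers the primary question does not use it. The same holds for the two stratification factors. When strata predict the outcome, stratified randomization balances them between arms, so the true sampling variance of the difference is reduced. The ordinary t-test still counts the between-stratum variance in its standard error, which therefore tends to be too large.

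Precision is at stake. Recruitment is described in the Discussion as possibly challenging, and the design has 80% power with no reserve at 75 evaluable patients per arm. The plan itself gives precision as the reason for adjusting, but applies the adjustment only to supporting analyses. It also leaves the technique for those analyses as an open choice, so more than one adjusted EpiTrack estimate could be produced under the same wording.

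**Working it through.** **Inputs.** From Sample size calculation: 75 per arm, 1:1 allocation, SD 4.70, difference 2.16 points (2.16 / 4.70 = 0.46 SD), two-sided alpha 0.05, power 0.80. The correlation r between preoperative and 12-month EpiTrack Junior is not in the document. It is assumed, and 0.3, 0.5 and 0.7 are shown.

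**Step 1: reproduce the plan's figure (unadjusted).**
- Standard error of the difference = 4.70 × sqrt(2/75) = 0.767.
- 2.16 / 0.767 = 2.81, and 2.81 − 1.96 = 0.85, which gives power 0.804 by the normal approximation.
- With the noncentral t, power is 0.798 and the detectable difference is 2.164.

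The stated 75 per arm, 2.16 points and 80% are therefore correct for the unadjusted test.

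**Step 2: effect of adjusting for the baseline score.** A linear model of the 12-month score on arm and baseline score has residual SD = 4.70 × sqrt(1 − r²). The proportion of outcome variance removed is r². Power follows by putting the residual SD into step 1 (for example, r = 0.5: 4.70 × 0.866 = 4.07; SE 0.665; 2.16 / 0.665 = 3.25).

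| Assumed r | Variance removed | Residual SD | Power at 75 per arm (normal / t) | Detectable difference (t-based) | n per arm for 80% power | 95% CI half-width |
|---|---|---|---|---|---|---|
| none (t-test) | 0% | 4.70 | 0.804 / 0.798 | 2.16 | 75 | 1.50 |
| 0.3 | 9% | 4.48 | 0.839 / 0.834 | 2.06 | 68 | 1.44 |
| 0.5 | 25% | 4.07 | 0.901 / 0.898 | 1.87 | 56 | 1.30 |
| 0.7 | 49% | 3.36 | 0.976 / 0.975 | 1.55 | 38 | 1.07 |

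The detectable difference is 2.164 × sqrt(1 − r²). The sample sizes and half-widths use the normal approximation. Any further gain from IQ stratum and center is not counted, because the document gives nothing from which to size it.

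**Step 3: does propensity weighting serve the stated purpose?** A simulation with 75 per arm, SD 4.70 and 3,000 runs per setting compared the empirical standard error of the arm difference under three methods. The propensity score was estimated from the baseline score.

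| Assumed r | t-test | Linear regression on baseline | Propensity weighting |
|---|---|---|---|
| 0.3 | 0.753 | 0.728 | 0.728 |
| 0.5 | 0.760 | 0.664 | 0.664 |
| 0.7 | 0.773 | 0.547 | 0.547 |

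Weighting by an estimated propensity score gains as much here as regression does.

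**The case against.** The case for leaving the plan alone is substantial, and most of it stands.

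- **The test is valid.** Under 1:1 randomization the t-test is unbiased, and ignoring the strata makes it conservative. The sample size was calculated for this test and reproduces. A reader might infer that the trial is underpowered or that its type I error is inflated; the document supports neither.
- **Baseline is not ignored.** Adjusted linear regression is planned for every analysis, expressly for precision, and mixed models of change are planned too. It would be wrong to say that the plan throws the baseline data away. Only the rank of the adjusted analysis is in question.
- **There is a stated hierarchy.** A reader might infer that no analysis is primary and that the result can be picked afterwards. Outcome parameters assigns the cross-sectional comparison to the primary question, and Statistical analysis calls the adjusted analyses additions. What is open is narrower: the alternative test if the distribution requires it, and the choice between two adjustment techniques.
- **Propensity scores are not misused.** One might object that randomization leaves no confounding to remove. The plan does not claim otherwise; it invokes precision, and step 3 shows that such weighting can deliver it. Inverse variance weighting is the looser term, since as usually understood it weights estimates by their precision and does not adjust patients for baseline.
- **The gain may be modest.** Baseline may be up to 3 months before surgery and the outcome up to 14 months after it, so up to 17 months apart, with surgery and, in one arm, drug withdrawal in between. A low r is plausible.
- **Detail may sit elsewhere.** An article need not list every covariate or the handling of small centers, so their absence is not held against it.

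One part of the point survives all of this. The article does fix which comparison answers the primary question, and it fixes the less efficient one when the better one is already planned.

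**Conclusion.** The point holds as an efficiency weakness that should be fixed. The primary comparison is valid, mildly conservative and correctly powered, but it leaves out a baseline measure and stratification factors that the trial already collects. The loss equals r² of the outcome variance: 9%, 25% or 49% for r of 0.3, 0.5 or 0.7. Power at 75 per arm would be about 0.83-0.84, 0.90 or 0.98 instead of 0.80. These figures assume a linear relation, SD 4.70 at 12 months and complete baseline scores. Calling the loss large is fair only from about r = 0.5 upward, and the document does not show where r lies.

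**What to change.** 1. Under Outcome parameters, name one primary analysis: linear regression of the 12-month EpiTrack Junior score on arm, preoperative EpiTrack Junior score, preoperative-IQ stratum and center, with small centers pooled or center fitted as a random effect.
2. Keep the independent-samples t-test as a sensitivity analysis.
3. Under Statistical analysis, replace the open choice in "we will use propensity score methods or inverse variance weighting methods" with this named model for the primary outcome.
4. Leave the sample size as it is. The unadjusted calculation is then a conservative basis, and any gain from adjustment is a reserve against slow recruitment or dropout.

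The cost is wording only. All the covariates are already collected, and Trial status reports that no patient had been included, so the change can be made before any outcome data exist.
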